## **3. Monitoring and Quality Assurance**

A standardized system of quality assurance of field procedures and data capture will be instituted. This will be based on daily checks of field procedures, written reports and data entry checks. To ensure proper implementation of the intervention, the study field supervisors will make spot checks and will arrange monthly refresher group sessions of project staff in which the problems encountered will be discussed and resolved. In addition, a 3% sample will be re-interviewed within two days of the initial visit.

Besides quality assurance procedures implemented by the program staff, the monitoring visits will also be conducted by senior project staff, District Coordinator of the LHW program and the

Executive District Health Officer (EDO) District Rahim Yar Khan. During these visits they will record and ensure that:

1. The quality of content, attendance of these trainings;
2. Field activities are going as planned and provide feedback;
3. LHWs are attending deliveries along with TBAs and also managing the newborns immediately after birth and giving them proper referral, if required;
4. The trained health facilities personnel are managing the sick mothers and newborns according to the standard protocols;
5. Availability and stock of the drugs (esp. injection ampicillin and gentamicin) and other supplies through random checks;
6. TBAs and LHWs are well versed in proper interventions or there is any need of refresher;
7. LHWs/TBAs are counseling the family/mother for early breast feeding, maintaining temperature of LBW babies

#### **Q. Ethical Considerations:**

##### ***Study Design Issues***

We have chosen a cluster randomized trial design. This is the most scientifically robust method of assessing comparative public health interventions as compared to other methods such as employing historical controls or using different populations. We do not believe that this design poses any major ethical dilemmas, as the “control” or “intervention” group will continue to receive all the current interventions in place within the primary care program of the government, namely those provided through the Lady Health Workers. In addition, the referral pathway throughout study area will be strengthened. A possible issue is one of contamination and a demand from control areas for interventions. Given the location of these clusters, we will try to minimize this possibility and if it occurs, this will be documented. We are also working to ensure that health facilities are staffed with qualified personnel although the appointment and retention of staff in public health facilities is beyond the control of the project investigators.

##### ***Ethical Review Committee (ERC)***

The ethical clearance for the entire project would be requested from the Ethical Review Committee at the Aga Khan University. This will be forwarded to Funding agency.

##### ***Informed Consent Issues***

The investigators will obtain verbal informed consent from all representatives of the communities involved in this study. In addition to these community representatives, we intend to obtain and document verbal community consent from all villages that are participating in this study. The consent will explicitly outline the aims and objectives of the study along with the strict confidentiality of the information provided. In all cases where the newborn is sick, but the parents choose domiciliary care over referral, a written informed consent will be obtained. The informed consent forms describe that participation is voluntary and can be terminated at any time without reason. The scope of the trial is explained. In addition, the parent/guardian will receive information on alternate sources of care same will apply in case of mother is sick and in this case she will give the consent. By agreeing (by signing, when appropriate) to the informed consent form, the parent/guardian confirms the child's or mother confirms her voluntary

participation and their intention to follow the study protocol and the instructions of the investigators.

### **Environmental consideration**

The study anticipate the following Environmental considerations during the flow and implementation of the project:

- The main target audience and beneficiary of this project is the women which usually do not have a say in the decision making and cannot have choices for her to opt for a better treatment. The women usually depend upon the decisions being made by the husbands and elders as the society is male dominant. We have attempted to take care of this factor to maximize the uptake of intervention and services by developing the community support groups.
- The Lack of commitment of the Public Health facility staff and LHWs can largely influence the success of the project. A major factor in sustaining relationships within the local partners is the use of collaborative principles. We will encourage trusting relationships in which there is recognition of the inherent value of all partners' perspectives. We plan to have relationships that foster open communication, development of shared history, coherence of goals, an honest exchange of ideas, and resolution of conflicts which all can contribute to a successful outcome.

### **R. Research communication and dissemination**

At the end of one year of intervention, interim analysis will be undertaken. This interim analysis will focus on relative difference in intervention arms on key study outcomes (morbidity and mortality and process indicators. Findings shall be shared with RAF (along with the formal report) and will be disseminated to stakeholders/ consumers, NGOs, research institutions, government agencies and donor agencies.

The same plan of research communication and dissemination will be repeated on the completion of the study. However, we will make sure to engage and update our stakeholders frequently in following ways

**Target Audience:** Stakeholders/users (Community groups, NGOs, Research institutions, Government agencies, donor agencies).

We will plan following dissemination activities.

- Research dissemination meetings at district and provincial level involving representatives of community health committees, district level stakeholders, political leaders, civil society organizations
- Sharing of the study reports with MNCH programme and LHW programme both at district and provincial level
- Development of position statements and policy papers at district & provincial level
- Engagement of key stakeholders and actors and build new constituencies of support at district as well as provincial level

- Disseminate and share the evidence with policy makers and stakeholders at provincial level to incorporate in the future provincial policies.

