### Quantitative approach:

**Cluster randomized control trial** will be used to evaluate the impact of EmONC package for maternal and neonatal health care delivery through community level health care providers. Clusters will be identified and matched on population size, socio-economic status (including structure, electricity, drinking water with HH density), birth/death rates, and number of functional LHWs and CMWs. Cluster Paired randomization will be done to allocate one group (intervention/control) to each cluster and all the LHWs in one union council will be assigned to one group to avoid any sort of contamination.

**Sample Size Calculation:** We are considering Union Council as a cluster. Each Union council serves approximately 15000 - 20000 population and usually contains a Basic health Unit which provides basic facilities of antenatal, natal and post natal care.

- We assume that the average cluster size is 15000 and considering a crude annual birth rate of 20 per 1000 and the estimated average perinatal mortality rate of 60/1000 with a coefficient of variation between clusters of 0.125 and to detect a 25% reduction in the mortality rates, we would require **20 Clusters** in total. Ten clusters per arm to provide the study with a power of 90% over a three-year intervention period.

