### **Study Outcome & Process Indicators (at the end of each yr (total 3)**

The primary outcome variables will be:

- All cause neonatal mortality rate
- Perinatal mortality rate

Secondary outcomes

- All cause maternal mortality
- Cause specific maternal mortality such as deaths related to postpartum hemorrhage, puerperal sepsis, eclampsia, obstructed labor, unsafe abortion and indirect causes
- Maternal morbidity such as (including obstetric fistula, eclampsia and obstetrical sepsis
- Cause specific neonatal mortality such as deaths related to birth asphyxia, prematurity, and sepsis.

The key process indicators include:

1. Proportion of women attended by CMWs/LHWs for ANC

2. Proportion of women supplemented with iron/folate
3. Proportion of women received TT immunization
4. Proportion of births attended by CMW
5. Proportion of births in which LHW was present
6. Proportion of women delivered at institution
7. Proportion of deliveries attended by TBAs
8. Proportion of clean delivery kits used
9. Proportion of women with high-risk pregnancy received referral
10. Proportion of women stabilized or managed before shifting to referral facilities.
11. Proportion of women received comprehensive EmOC services among those who were referred
12. Proportion of newborns seen by CMWs/LHW around day 1, 3, 7 and 28
13. Proportion of newborns resuscitated by CMWs, LHWs and TBAs respectively
14. Proportion of CMWs/LBW able to manage hypothermia
15. Proportion of neonates breastfed in an hour of birth
16. Proportion of neonates avoided pre lacteal feeds
17. Proportion of neonates delayed bathing for at least 6 hours
18. Proportion of neonates who received emollient application
19. Proportion of community participated in support group

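### Between-arm mortality results are to be released to outside stakeholders after year 1, while two years of the trial remain

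*Protocol*

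**What the plan says.** Protocol, section R (Research communication and dissemination): "At the end of one year of intervention, interim analysis will be undertaken". The "interim analysis will focus on relative difference in intervention arms on key study outcomes", which the text spells out as morbidity, mortality and process indicators. The trial has one intervention and one control group, so this can only mean intervention against control.

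The same paragraph continues: "Findings shall be shared with RAF (along with the formal report) and will be disseminated to stakeholders/ consumers, NGOs", followed by research institutions, government agencies and donor agencies. The plan is to be repeated at completion, so the year-1 release is meant to be as wide as the final one. The target audience listed next includes community groups. The activities for keeping stakeholders updated include "Sharing of the study reports with MNCH programme and LHW programme both at district and provincial level".

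Protocol, Quantitative approach (sample size): "Ten clusters per arm to provide the study with a power of 90% over a three-year intervention period". Two years of intervention and follow-up therefore remain at the interim.

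Protocol, Study Design Issues: "A possible issue is one of contamination and a demand from control areas for interventions". The protocol says it will try to minimise this and will document it if it happens.

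The outcomes section, which lists neonatal and perinatal mortality as the two primary outcomes, is headed "Study Outcome & Process Indicators (at the end of each yr (total 3)".

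**The concern.** In a trial where clusters know their allocation, comparative mortality results are normally withheld until follow-up ends, because those who deliver, receive or record care can act on them. Here the plan does the reverse in explicit terms.

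Some of the named recipients stand close to the comparison. Control clusters keep their usual care through the Lady Health Worker (LHW) programme, and that programme is on the list for study reports. Community groups are part of the audience. The programme's district coordinator also makes monitoring visits to the trial (Monitoring and Quality Assurance). A favourable year-1 result could raise demand in control areas or shift effort by health staff. An unfavourable one could weaken uptake in intervention areas. Either could affect how events are reported. Years 2 and 3, which supply two thirds of the births, would then no longer compare the package with undisturbed usual care.

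A second issue is what stakeholders would be given: a comparison that the sample-size calculation was not built to support after one year.

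**Working it through.** **1. The text.** No arithmetic is needed for the release itself. Section R fixes the timing (one year), the content (arm difference in mortality and morbidity) and the recipients. The sample-size paragraph fixes the duration (three years). The document states no confidentiality limit and no independent body to receive the interim result. No blinding is described, and support groups, training workshops and phone messages could hardly be concealed.

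**2. Inputs for precision (Quantitative approach).** Population 15,000 per cluster × 20 births per 1000 per year = 300 births per cluster-year, or 900 over three years. Control perinatal mortality p0 = 0.060; 25% reduction, so p1 = 0.045; difference d = 0.015. Between-cluster coefficient of variation k = 0.125. Ten clusters per arm. No significance level is stated; two-sided 5% is assumed.

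**3. Reproducing the planned power.** The usual formula for unmatched clusters is

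c = 1 + (1.96 + 1.282)² × V / d², with V = [p0(1−p0) + p1(1−p1)]/m + k²(p0² + p1²).

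- m = 900: V = 0.099375/900 + 0.015625 × 0.005625 = 1.983 × 10⁻⁴.
- c = 1 + 10.507 × 1.983 × 10⁻⁴ / 2.25 × 10⁻⁴ = 10.26 per arm.
- Power with c = 10: Φ(√(9 × 2.25 × 10⁻⁴ / 1.983 × 10⁻⁴) − 1.96) = Φ(1.24) = 89%.

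The stated 90% with ten clusters per arm is therefore reproduced, as a single 3-year test on one outcome.

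**4. The same design at year 1.**

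- m = 300: V = 0.099375/300 + 0.015625 × 0.005625 = 4.19 × 10⁻⁴.
- Power: Φ(√(9 × 2.25 × 10⁻⁴ / 4.19 × 10⁻⁴) − 1.96) = Φ(0.24) = 59%. Using the matched-pair correction instead gives 54% at year 1 and 85% at year 3.
- 95% half-width: 2.101 (t, 18 df) × √(4.19 × 10⁻⁴ / 10) = 0.0136, that is 13.6 per 1000 around a planned difference of 15 per 1000.
- In relative terms, a true rate ratio of 0.75 would carry a 95% interval of about 0.59 to 0.96.

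So if the package works exactly as planned, about 4 in 10 year-1 reports would be non-significant. In simulation the significant ones overstate the effect, with a mean rate ratio of about 0.70 against a true 0.75.

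**5. Secondary check: false-positive risk.** Null trials were simulated for the two analyses that the protocol describes (year 1, and cumulative data at year 3), with an unpaired cluster t-test at an assumed 5% level. Neonatal mortality was taken as 55 per 1000 with 75% in the first week (background figures in the protocol), giving an assumed split of 41 early and 14 late deaths, and 60 − 41 = 19 stillbirths.

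| Rule for claiming success | Chance of a false claim |
|---|---|
| Perinatal mortality, year 3 only | about 5% |
| Perinatal mortality, year 1 or year 3 | about 8.5% |
| Either primary, year 3 only | about 7.5% |
| Either primary, year 1 or year 3 | about 13% |

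With k between 0 and 0.25 the second row runs from about 8% to 9% and the last from about 11% to 15%.

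**The case against.** The strongest reply is that the harm from release is asserted and not measured. The package rests on multi-day training, phones, kits, support groups and transport funds, which a control area does not acquire by hearing a result. Facility strengthening already goes to both arms. The surveillance teams work independently of the LHWs and are not listed as recipients. The protocol undertakes to minimise and document contamination. All of this limits the likely damage, and it rules out saying that the release would create control-area demand, or that every listed body runs or receives control services. It does not remove the risk: care-seeking, staff effort and reporting can shift without the full package, nothing shields the data collectors from results that are widely circulated, and documenting contamination does not undo it.

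A reader might also infer a stronger charge: that the primary outcomes are tested every year with no error control. The document does not support this. The yearly reading comes from a heading over outcomes and process indicators, and names no test. Only the year-1 and final analyses are described. There is no year-2 test, no separate test of each year's data, no stopping rule and no provision to claim success early. Interim boundaries and multiplicity rules may sit in a statistical analysis plan that is not at hand. If the 3-year test is the confirmatory one, looking earlier leaves its error at about 5%.

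**Conclusion.** The point holds for the release. The protocol itself commits to giving between-arm mortality and morbidity results to a wide outside audience with two of three years to run, in a trial with no blinding described and with control-area demand already named as a risk. A statistical analysis plan would not undo that commitment. The direction and size of any resulting bias cannot be computed from the document.

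What can be computed is how weak the released evidence would be: about 59% power and a half-width of about 13.6 per 1000 around a planned 15 per 1000. Both rest on the protocol's inputs, an assumed two-sided 5% level and an unmatched cluster analysis.

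The false-positive figures are secondary and conditional. About 8.5% (perinatal mortality) and about 13% (either primary) apply only if success could be claimed at year 1 or year 3. Of the 13%, about 7.5% arises from testing two primary outcomes at the end only and has nothing to do with the interim.

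**What to change.** Reword section R so that the year-1 report released outside the trial contains only arm-pooled rates and implementation indicators. If a comparative year-1 look is wanted, say that it is confidential and who may see it; an independent committee is one option. State that the 3-year comparison is the single confirmatory analysis, and add to the outcomes section that the yearly readings are descriptive.

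This changes wording only, with no effect on sample size, data collection or the interventions. The cost is that the funder and stakeholders still get a year-1 report but wait until the end of the study for between-arm mortality results.

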### **S. Anticipated Utilization or Implications:**

It is anticipated that the study will offer a strong message, particularly to policymakers at provincial level, about the need for an integrated approach to develop and implement MNCH

#### **Local level**

- We anticipate that awareness regarding maternal and newborn care will increase at individual, family and community levels. This may potentially improve care-seeking for maternal and newborn care.
- We anticipate that this project will increase our understanding of the mechanisms to link the health system and community through community health workers within a functional referral system.

#### **National Level**

- Given the burden of maternal and newborn care in Pakistan, the successful outcome of this project will yield information that will be of great value to future training programs for community health workers, and can be replicated in other parts of the country.
- The project will also yield information that will help in determining the balance of community-based and facility-based programs for reducing the burden of postpartum maternal and neonatal complications.
- This project will specifically provide information that will link the maternal and neonatal care components of the existing interventions in this area.
- This project will help in capacity development for partner groups. It's a tailor made process which seeks to strengthen the effectiveness and impact of our program of postpartum maternal and neonatal care.

#### **Global Level**

- Maternal and neonatal complication forms a major proportion of maternal and newborn deaths globally. This project will thus provide information that may be of great importance to other health systems and circumstances where a large proportion of births take place in domiciliary settings in the hands of primary care health workers.

